#### Hypotheses

The analyses will test the two primary hypotheses and four secondary hypotheses. The primary hypotheses are that, over the 12-month follow-up period, clients in the SBIRT group will be 1) more likely to reduce their level of drug use and 2) more likely to reduce their level of alcohol use compared with clients in the control group. The secondary hypotheses are that, over the 12-month follow-up period, clients in the SBIRT group will be 1) more likely to participate in brief treatment and/or longer-term treatment and to participate in AA, NA, or other self-help groups; 2) less likely to be arrested and incarcerated; 3) more likely to have a higher quality of life; and 4) less likely to engage in HIV risk behaviors compared with clients in the comparison group.

#### Research questions

The study will also examine several research questions related to participation, implementation, and cost:

Participation

1. How many inmates agreed to be in the study? What reasons were given for any refusals?

2. Of those assigned to the SBIRT group, what percentage was screened?

3. Of those screened, what percentage scored at each risk level?

4. Of those who scored at moderate or high risk, what percentage participated in brief treatment and/or longer-term treatment?

5. What was the level of satisfaction with the type of intervention received?

Implementation

6. What problems were encountered in setting up and implementing SBIRT in a jail setting?

7. What problems were encountered in recruiting participants and in delivering the intervention?

Cost

8. How much does it cost to provide the SBIRT intervention to men and women inmates?

#### Preliminary analysis

Equivalency between study groups will be examined on baseline characteristics that are correlated with outcomes. Attrition bias will be examined using baseline characteristics to compare those who complete follow-up with those who do not. Oral-fluid test results will be used to assess the validity of self-report of drugs and alcohol. Records data will be compared with self-report on treatment participation and criminal justice involvement.

#### Missing data

The main strategy to reduce missing data will be to train and monitor interviewers to ensure that all questions are answered. In analyses, missing data will be explored through frequency distributions. Missing data will be addressed using maximum likelihood (ML) or multiple imputation (MI) estimates for incomplete data [45,46]. Alternatively, statistical techniques that allow for missing data may be used (e.g., generalized linear models).

#### Hypothesis testing

Data from the baseline and the 12-month follow-up interviews and from records will be used to test the hypotheses. Analyses will be based on the intent-to-treat principle. Primary outcome 1 for drug use and primary outcome 2 for alcohol use, measured as dichotomous outcomes at follow-up, will be tested using chi-square analysis. Measured as change over time, the two hypotheses will be tested using repeated measures Generalized Estimating Equations (GEE) modeling, available in SAS proc GENMOD [47]. If the two groups differ significantly at baseline on drug or alcohol use variables or on other variables, logistic regression analysis will be used to assess the group effect for the drug and alcohol use outcomes, controlling for the covariates. Secondary outcome 1 for participation in treatment and self-help groups will be measured as a dichotomous variable and will be analyzed using either chi-square or logistic regression analysis. For secondary outcome 2 on arrest and incarceration, Cox proportional hazards regression [48] will be used to analyze the group difference in terms of elapsed time to re-arrest and re-incarceration. For secondary outcome 3, quality of life, the score on the WHO Quality of Life measure is continuous and will be analyzed using t-tests or, if baseline covariates need to be controlled, a multiple regression model. The outcome for secondary outcome 4, HIV risk behavior, will be measured as involvement in total number of risky behaviors and will be analyzed using a *t*-test or, if there is a need to control for baseline variables, by using a multiple regression model.

For the primary outcomes, an effect size will be calculated. The index of effect size will be the standardized mean difference (calculated as the difference between the means on the outcome variable for the two groups divided by the pooled standard deviation); for proportions, the equivalent effect size is calculated using the arc sine transformation [49]. Effect sizes will provide a quantitative measure of the magnitude of the difference between groups; they will also be useful in calculating power for future studies of SBIRT.

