### Power analysis for sample size

Average effect sizes from meta-analyses of brief interventions for alcohol problems [30-32] range from a standardized mean difference of 0.18 to 0.43. Although no meta-analyses have been conducted on brief interventions for drug problems, effect sizes from primary studies involving illicit drugs [9-11,14,33] range from 0.13 to 0.84. Most of these studies focus on clients in primary care or other health-care settings. No experimental studies have reported outcomes for SBIRT (as opposed to brief intervention) with offenders. Since previous research provides limited guidance for estimating the expected effect sizes for the primary outcomes of the study, it seems reasonable to assume a small effect size; that is, a standardized mean difference of about 0.20 for a reduction in alcohol and drug use from baseline to 12-month follow-up. The power analysis (using the RMASS2 program; [34]) assumes alpha = 0.05 (two-sided), power = 0.80, an attrition rate of 15%, and an autoregressive variance-covariance structure, with a moderate correlation of 0.50 between levels of use at baseline and follow-up. With an expected effect size of 0.20 for the primary outcomes, the sample size is 778, equally divided between the two study groups. This estimate is similar for different variance-covariance structures, including a random-effects structure. We set the total sample at 800. To assess possible treatment by gender interactions, the sample recruited will include 25% women.

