### Tracking and locating for 12-month follow-up interviews

At baseline, the interviewer will ask participants to fill out a Locator Form. This form contains information that is useful for locating participants for follow-up interviews (e.g., driver’s license; names, addresses, and phone numbers of immediate relatives and unrelated friends; areas of town frequented; locations where social services are received; and probation or parole officer contacts). Other tracking resources include local and state correctional agencies that maintain publicly available websites that can be searched to determine whether a subject is in jail or prison or is on probation or parole. We will use a program developed in FileMakerPro^®^ for previous ISAP studies to record information needed for the tracking and locating process (e.g., locator data, agency contacts, letters, telephone calls, appointments). Tracking and locating procedures are described in a manual that was developed at ISAP [42] and is widely distributed by NIDA and CSAT. These procedures have been used by ISAP researchers in many studies to track and locate subjects for as long as 10 years between interview points, with follow-up rates typically at 85% or more [43]. Follow-up interviews have been conducted with subjects who are homeless, who are in jail or prison, who have absconded from probation or parole supervision, or who reside in other states or countries. In short, we expect that the detailed locator information from participants and the successful strategies used in previous studies will enable us to locate 90% of the baseline sample and, allowing for refusals and deaths, to interview at least 85% of the sample at the 12-month follow-up. We will obtain criminal justice and treatment records covering the 12-month follow-up period on all participants.

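### Each primary outcome has two unranked analyses (chi-square at follow-up, GEE on change), and only the change form matches the quantity the trial was sized on

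*Protocol article*

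**What the plan says.** The Hypotheses section announces a short list: "The analyses will test the two primary hypotheses and four secondary hypotheses". The two primary ones concern drug use and alcohol use.

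The Hypothesis testing section then gives each of them two analyses in consecutive sentences. The outcomes, "measured as dichotomous outcomes at follow-up, will be tested using chi-square analysis". Next: "Measured as change over time, the two hypotheses will be tested using repeated measures Generalized Estimating Equations (GEE) modeling". A third route follows: if the groups differ significantly at baseline on substance use or other variables, logistic regression with covariates is used for these outcomes. None of the three is called primary, decisive or supportive.

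The Power analysis for sample size section rests on "a standardized mean difference of about 0.20 for a reduction in alcohol and drug use from baseline to 12-month follow-up", "with a moderate correlation of 0.50 between levels of use at baseline and follow-up", and "assumes alpha = 0.05 (two-sided), power = 0.80, an attrition rate of 15%, and an autoregressive variance-covariance structure". It gives 778 participants, rounded up to 800. It contains no event proportions and no calculation for a dichotomous outcome. The 0.05 appears here only; no level is attached to the tests themselves.

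**The concern.** The two analyses answer different questions. The chi-square test compares 12-month status and makes no use of baseline. The GEE analysis compares change from baseline. They can disagree, and the article has no rule for that case.

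Two things follow. A positive finding could be reported from whichever form favours SBIRT, which raises the chance of a false claim for each outcome. Conversely, if the chi-square test is treated as decisive, a null result could be taken as evidence from a trial with 80% power, although the power calculation was not done for that test.

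**Working it through.** **Inputs from the article.** Two-sided alpha 0.05; power 0.80; attrition 15%; standardized mean difference 0.20; baseline to follow-up correlation ρ = 0.50; 800 recruited, allocated equally. Analysed per arm: 400 × 0.85 = 340.

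**Inputs assumed.** The cut-point and control-group rate of the dichotomised outcome, the drug–alcohol correlation, and the correlation between the two tests of one outcome. The article gives none of these, so ranges are shown.

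**1. The plan's own figure.** The variance of a change score, in units of the level's variance, is 2(1 − ρ) = 2(1 − 0.50) = 1. Per arm, n = 2(1.960 + 0.842)²/0.20² = 393, or 786 in total. That is close to 778, but with no attrition. With 15% attrition it becomes 786/0.85 = 925; a two-time-point longitudinal contrast with loss at follow-up only gives 858. So 778 is not reproduced under these readings. The settings used in the sample-size program are not given, so it is not shown to be wrong either. The present point does not depend on it. What matters is that the calculation concerns a mean reduction from baseline.

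**2. False-positive rate if either result may be claimed, each at 0.05.** Four independent tests: 1 − 0.95⁴ = 18.5%. Two independent tests: 1 − 0.95² = 9.75%. The tests are not independent, because both analyses of an outcome use the same 12-month data. Simulated from a multivariate normal, with drug–alcohol correlations of 0 to 0.5:

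| Correlation between the two tests of one outcome | One outcome, either test | Any of four tests |
|---|---|---|
| 0 | 9.7% | 17.3–18.5% |
| 0.4 | 9.4% | 16.6–17.8% |
| 0.5 | 9.1% | 16.2–17.3% |
| 0.7 | 8.3% | 14.9–16.0% |
| 0.9 | 7.0% | 12.6–13.7% |
| 1 (versions coincide) | 5% | 9.0–9.8% |

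Where a trial falls depends on how the GEE model uses baseline. For an unadjusted change score against a median split at follow-up, the correlation is √((1 − ρ)/2) × √(2/π) = 0.50 × 0.798 = 0.40. If the change model effectively adjusts for baseline, it is √(1 − ρ²) × 0.798 = 0.866 × 0.798 = 0.69. A direct data simulation (20,000 null trials, 340 per arm, ρ = 0.50, median split, drug–alcohol correlation 0.3) gave a test correlation of about 0.41 and 17.6% for any of four.

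**3. Power of the chi-square test at 340 per arm.**

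- If the arcsine effect is taken as h = 0.20: Φ(0.20 × √170 − 1.96) = Φ(0.648) = 0.74.
- If a 0.20 SD shift in a normal score is dichotomised:

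| Control rate | SBIRT rate | Power |
|---|---|---|
| 50% | 42.1% | 0.55 |
| 30% | 23.4% | 0.49 |
| 20% | 14.9% | 0.42 |
| 80% | 73.9% | 0.47 |

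**4. Power of the continuous forms at 340 per arm.**

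- Unadjusted change: Φ(0.20 × √170 − 1.96) = 0.74.
- Level at follow-up adjusted for baseline, residual SD √(1 − 0.50²) = 0.866: Φ((0.20/0.866) × √170 − 1.96) = Φ(3.011 − 1.960) = 0.85.
- The same at alpha 0.025: Φ(3.011 − 2.241) = 0.78.

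**The case against.** The strongest reply is that this is a journal article. Ranking of analyses and multiplicity handling often sit in an analysis plan, which is not shown here. That disposes of one stronger reading, that the absence of an alpha adjustment is itself the error. It does not dispose of the point: the article positively prescribes two tests for each outcome, and a later plan that chose one would have to depart from this text.

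A reader might also infer that the trial runs four tests, all at 0.05, with a familywise error of about 18%. The article supports less. It attaches 0.05 only to the power analysis and has no rule that any one success counts. The 18.5% needs independence. About half of the any-of-four figure comes simply from having two primary hypotheses, and whether two separately stated hypotheses must share alpha is debatable.

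A reader might further infer that the chi-square test has only about 55% power or less. That depends on dichotomising a shifted normal score. The Hypothesis testing section treats the arcsine index as the counterpart of the standardized mean difference, though for reporting. At h = 0.20 the chi-square test has 74% power, the same as an unadjusted change test. The loss is therefore possible, not demonstrated.

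Finally, the phrase about being more likely to reduce use might be read as a third, responder-type endpoint. The article uses the same phrasing for quality of life, which it analyses as a continuous score, so this is loose wording and carries no weight.

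**Conclusion.** The point holds in a limited form. Each primary outcome has two prescribed, unranked analyses plus a significance-triggered third, and only the change form concerns the quantity that the sample size was based on.

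If each test is run at 0.05 and either result may be claimed, the false-positive rate is about 8–10% per outcome (7% if the two tests correlate at 0.9). Across both outcomes it is up to about 18%, roughly 13–18% for plausible correlations. The logistic regression route is not counted in these figures.

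The stated 80% power is not shown for the chi-square test: 42–55% or 74% at 340 per arm, depending on what is assumed about the dichotomised effect. The article supplies none of the test correlations, the drug–alcohol correlation or the control rates, so these are ranges and not properties of the plan. Matching the sample-size basis also does not mean that the change form is confirmed at 80%, since 778 could not be reproduced with attrition included.

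**What to change.** 1. Name one primary analysis for each outcome: the 12-month level of use (for example the ASSIST drug or alcohol score, which the follow-up interview already collects), adjusted for its baseline value in all cases. With the stated inputs this has about 85% power at alpha 0.05.
2. Label the chi-square comparison supportive. Do the same for the oral-fluid results, and align the Variables section, which now counts biological testing within the primary outcomes. The tests are done at follow-up only, and not in participants interviewed in custody or by telephone, so they cannot measure change.
3. Drop the switch to logistic regression after a significant baseline difference. Adjustment specified in advance makes it unnecessary and removes a data-dependent choice.
4. State how the two primary hypotheses are interpreted. If they are separate claims, say so. If they share an overall 0.05, for example by Holm, restate the power as about 78% at alpha 0.025.

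The cost is wording, with no new data or participants. The downside is that a dichotomous result can no longer be claimed as primary, and that power falls from about 85% to about 78% if alpha is shared.

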#### Cost analysis

Cost analysis will focus on estimating and comparing total intervention costs for the SBIRT and the comparison groups. This will allow us to report both the total and incremental cost of SBIRT. The incremental cost is the additional cost (above the cost of services offered to comparison clients) of SBIRT. Specifically, we will calculate total annual cost, average weekly cost per client, and average cost per treatment episode for both groups. To highlight the relative contribution of the cost components, we will calculate the percentage of total annual cost accounted for by each cost category. The data analysis routines for the DATCAP have been used in prior studies [50,51].

#### Other analyses

Additional analyses, while not testing specific hypotheses, will address related topics of interest, such as differences in outcomes by risk level, stage of change, and readiness for treatment. Since such analyses may involve subgroups with insufficient cell size to meet power requirements, findings will be considered tentative.

## Discussion

The purpose, setting, and design of the study of SBIRT with jail inmates make it a pragmatic trial, as defined by Zwarenstein et al. [52], namely, a study with design choices that “maximise applicability of the trial’s results to usual care settings, rely on unarguably important outcomes such as mortality and severe morbidity, and are tested in a wide range of participants.” The study is expected to advance knowledge of SBIRT in several ways. First, virtually all of the evaluation and dissemination work on SBIRT has occurred in health-care settings, with little or no attention to the potential benefit of SBIRT for the large population of offenders, most of whom are at risk for drug and/or alcohol problems and for rearrest or supervision violation. Although a few studies have evaluated brief interventions with offenders, this study will examine the effectiveness of the full spectrum of SBIRT components. To our knowledge, this would be the first experimental study of the effectiveness of SBIRT with offenders. Second, whereas most previous research on SBIRT has focused on alcohol, the study will expand the relatively limited evidence base on the effectiveness of SBIRT with persons who use drugs (or drugs and alcohol). Third, the study supplements the brief intervention and the treatment referral components of SBIRT with a BT protocol for offenders who are at moderate risk or for those who are not willing to commit to longer-term treatment. Fourth, unlike most studies of SBIRT, this study will examine the effects of SBIRT on HIV risk behaviors. Finally, the study will collect needed information on the costs associated with providing SBIRT to an offender population. The study may face a number of challenges that may limit the validity or generalizability of the findings, although we will take steps to limit their effect.

### Recruitment

Given the large number of inmates being released from the jail each day, recruitment goals should be able to be met even with a relatively high refusal rate. But if numbers do fall short, we will identify reasons that inmates refuse participation and attempt to correct them, confer with jail staff to address any logistical issues, extend the recruitment period, or recruit at other county jail facilities.

### Randomization violations

The project director will closely monitor the randomization protocol to ensure the integrity of assignment (i.e., there are no crossovers from one group to another). Should problems occur, solutions will be discussed with research and counseling staff. Even if crossovers do occur, analyses of hypotheses will use the intent-to-treat principle.

### Attrition and self-report data

Every effort will be made to retain all participants in the study and to interview all participants at follow-up. Tracking and locating procedures described above should minimize attrition. Virtually complete data will be available for outcomes based on administrative records. Although there is often concern about the validity of self-report, prior research indicates that self-report interviews, when properly conducted, are generally reliable and valid in measuring drug and alcohol use [53,54] and criminal involvement [55]. The strategies discussed above will increase reliability and validity of self-report data.

### Research effects

A number of researchers [10,56-58] have noted that the intervention effects of brief interventions may be confounded with research effects—that is, research assessments may have a therapeutic effect for all subjects, thus diluting treatment effects. Although this study will not formally assess this possibility through manipulation, we do attempt to reduce the impact of research effects by limiting the amount of data collected at baseline.

### Generalizability

The study participants will probably not be typical of inmates who would be the intended population of SBIRT in routine practice. They are willing to participate in research activities, are compensated for their participation in research, and receive an intervention from carefully trained and monitored counselors. These necessary research conditions would not be present in a typical setting that provided SBIRT to offenders, and thus, the effects found may be attenuated in a “real world” setting.

## Conclusion

Screening, brief intervention, and referral to treatment provides a bridge between primary prevention and treatment by conducting early identification and intervention with people whose current use may be low but who are at risk for future alcohol and drug problems and by referring those with likely abuse or dependence to longer-term treatment. The public health assumption informing SBIRT is that individual reductions in alcohol and drug use, when aggregated over a large at-risk population, can have significant health, public health, and public safety effects [59]. As noted above, while SBIRT has been found to be effective in some health-care settings (and to a lesser extent in colleges and universities), little published research is available on the use of SBIRT to identify offenders at different risk levels and to provide appropriate levels of intervention. Should SBIRT prove effective with this population, it would offer a proactive approach to help offenders reduce drug and alcohol use, HIV risk behaviors, and criminal behavior and improve their psychosocial functioning. As such, the wider dissemination of SBIRT to criminal justice settings statewide or nationwide could have a significant impact on public health and public safety.
